## Abstract

**Background:**

Acute cholecystitis occurs frequently in the elderly and in patients with gall stones. Most cases of severe or recurrent cholecystitis eventually require surgery, usually laparoscopic cholecystectomy in the Western World. It is unclear whether an initial, conservative approach with antibiotic and symptomatic therapy followed by delayed elective surgery would result in better morbidity and outcome than immediate surgery. At present, treatment is generally determined by whether the patient first sees a surgeon or a gastroenterologist. We wish to investigate whether both approaches are equivalent. The primary endpoint is the morbidity until day 75 after inclusion into the study.

**Design:**

A multicenter, prospective, randomized non-blinded study to compare treatment outcome, complications and 75-day morbidity in patients with acute cholecystitis randomized to laparoscopic cholecystectomy within 24 hours of symptom onset or antibiotic treatment with moxifloxacin and subsequent elective cholecystectomy. For consistency in both arms moxifloxacin, a fluorquinolone with broad spectrum of activity and high bile concentration is used as antibiotic. Duration: October 2006 – November 2008

**Organisation/Responsibility:**

The trial was planned and is being conducted and analysed by the Departments of Gastroenterology and General Surgery at the University Hospital of Heidelberg according to the ethical, regulatory and scientific principles governing clinical research as set out in the Declaration of Helsinki (1989) and the Good Clinical Practice guideline (GCP).

**Trial Registration:**

ClinicalTrials.gov NCT00447304

## Background

### Medical problem

Acute cholecystitis is one of the most significant acute diseases in the Western World, and may be associated with only mild pain and nausea or become a severe, life-threatening illness due to complications. Acute cholecystitis is mainly caused by gall stones, whilst cholestasis is mainly associated with superinfection with bacteria, in general species of enterobacteria, enterococci, bacteroides and anaerobic streptococci [1].

The principal complication is recurrent biliary colic and cholestasis. The latter may lead to ascending cholangitis, and whilst this can be managed with antibiotics, other complications can not be cured conservatively, such as gangrenous changes, gall bladder perforation and biliary leakage, and acute necrotic gallstone pancreatitis [2-5]. Liver abscesses and underlying incidental carcinoma have also been reported in some cases [2,6].

The risk of developing second and subsequent episodes of acute cholecystitis is higher than the risk of suffering an initial episode [7,8]. Laparoscopic cholecystectomy is therefore usually recommended, but whether this should be performed immediately or after first giving antibiotic treatment to allow the acute condition to subside is controversial [9-12].

### Immediate surgery versus conservative procedure with subsequent elective surgery

The approach taken is often decided by whether the patient first sees a gastroenterologist, who favors conservative initial antibiotic therapy with later elective surgery, or a surgeon, who favors immediate surgery.

It is still unclear which approach is better in medical and health economic terms. The infection may not respond to conservative treatment on one hand, on the other hand surgical intervention while the disease is acute may increase complications, and conversion to open surgery may be necessary. It is unclear whether it is better to conduct early cholecystectomy, thereby avoiding the risk of recurrent cholecystitis or pancreatitis.

A meta-analysis by Papi et al. (2003) including 12 prospective randomized trials showed no significant difference for morbidity and mortality between immediate surgical intervention (laparoscopic or open) and elective surgery after the acute inflammation had subsided [13]. The numbers of patients and rates of complications were too low to enable any conclusions to be drawn. Also, their definition of "immediate" was between 1 and 7 days after disease onset, while the modern standard favors laparoscopic surgery within 24 hours of onset [14,15].

All studies in the meta-analysis had been performed between 1970 and 2000, and Papi concluded that new studies in an adequate number of patients to show statistical significance should be performed [13]. Two subsequent prospective randomized trials concerning the appropriate timing for surgery also failed to lead to conclusive results, except for a slightly shorter hospital stay in patients treated with immediate surgery [16,17].

In many centers early cholecystectomy is well established although the evidence is not yet conclusive. To our knowledge there has never been a study in which both specialties – gastroenterology and surgery – are equally involved.

### Choice of antibiotic

Moxifloxacin (Avalox^®^) covers the spectrum of gram-positive, gram-negative and anaerobic bacteria usually responsible for intra-abdominal infections [18-20]. It can be applied orally or intravenously in a single dose of 400 mg/day, resulting in bile concentrations significantly above the minimum inhibitory concentration [21], and 3–4 times higher than plasma concentrations [22].

A controlled double-blinded study in 379 patients in the USA showed moxifloxacin to be at least as effective as standard treatment by with piperacillin + tazobactam i.v. followed by oral amoxicillin+clavulanate in complicated intra-abdominal infections [23,24]. A European prospective randomized and controlled open-label study showed equivalent efficacy for moxifloxacin and ceftriaxone plus metronidazole (AIDA study) [25]. Moxifloxacin was effective and well-tolerated in both studies, with gastrointestinal disorders like nausea and diarrhea being the most frequent adverse events [26,27].

## Study Design

### Aim of the study

The objective of this trial is to compare the 75-day morbidity of two different approaches to the treatment of acute cholecystitis: (i) laparoscopic cholecystectomy within 24 hours of hospital admission; and (ii) initial antibiotic treatment with moxifloxacin followed by cholecystectomy in the infection-free interval (Day 7 to 45).

### Organization of the study

The trial is a GCP-compliant, multicenter, prospective, randomized non-blinded study. Patients with acute cholecystitis meeting the inclusion criteria are randomized to one of the treatment arms. The study is being audited by members of a contract research organization (CRO) and may be subject to government inspection. The trial was approved by the German authorities and Ethical committees.

### Number of patients needed

The primary aim of the study is to compare morbidity in the two groups 75 days after enrolment. A difference in morbidity of less than 10% is defined as equivalent. The null-hypothesis is /ρ_M1 _- ρ_M2 _/> 0.1, where ρ_Mi _is the morbidity rate of treatment group i. Complications are expected in 16% of patients in each group; each group therefore needs to enroll 273 patients to permit verification of the null-hypothesis with an α-error of 0.05 and a β-error at 0.15, yielding a power of 90%. Assuming a validity rate of 85%, 322 patients are required per group, resulting in a total patient sample of 644.

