## Discussion

All statistical tests will be performed two-sided with a level of significance of 5%. The patients will be analyzed as treated. The principle analysis will be on evaluable patients and a supportive intent-to-treat analysis will be performed. Patients will be stratified according to severity of their condition (ASA ≤ 2 vs. ASA > 2); the principle analysis will be stratified, but a non-stratified analysis will also be performed

The groups will be tested for equivalence of distribution of age, sex and body mass index. The analysis will be conducted using analysis of variance with the factors study group and severity of disease, stratified by the Cochran-Mantel-Haenszel test.

95% confidence intervals (CI) for the difference of morbidity rates will be calculated. If and only if this CI lies between -10% and +10% the two procedures will be considered equivalent. The calculation of the 95% CI will be stratified by severity (ASA ≤ 2 vs. ASA > 2). A Breslow-Day test will be performed to check for homogeneity between these two strata.

Amongst the secondary variables, the mean morbidity score in the two groups stratified by severity of disease will be compared using the Wilcoxon rank-sum test. Where appropriate, descriptive statistics will also be performed for all other variables.

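### A β of 0.15 cannot give 90% power, and under the plan's own 95% CI equivalence rule 273 evaluable patients per group give 78%

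*Protocol article*

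**What the plan says.** All the design inputs are in the Protocol article, section Number of patients needed. The margin is set there: "A difference in morbidity of less than 10% is defined as equivalent". The assumed rates are equal: "Complications are expected in 16% of patients in each group". The resulting size follows: "each group therefore needs to enroll 273 patients", said to be enough "with an α-error of 0.05 and a β-error at 0.15, yielding a power of 90" per cent. An assumed validity rate of 85% then raises 273 to 322 per group, 644 in all.

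The decision rule is in the section headed Discussion, which holds the statistical methods. It states "All statistical tests will be performed two-sided with a level of significance of 5" per cent, then "95% confidence intervals (CI) for the difference of morbidity rates will be calculated", and then the criterion itself: "If and only if this CI lies between -10% and +10% the two procedures will be considered equivalent". The same section makes evaluable patients the principal analysis set, so 273 per group, not 322, is the number that carries the power.

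**The concern.** There are two separate faults. First, β and power are complements, so a β of 0.15 and a power of 90% cannot describe one calculation. Second, the equivalence rule has two margins to clear, and a 95% interval tests each at one-sided 2.5%. A calculation that looks at one margin only, or that spends 5% on each, gives a higher power than this rule delivers. The α of 0.05 in the sample-size section does not say whether it applies per margin or two-sided, so it does not settle which calculation was meant.

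This is the primary endpoint and the only equivalence criterion in the plan. If power is overstated, the trial is more likely to end without a conclusion than its planners believe. A reader who trusts the 90% may then take failure to show equivalence as a sign that the approaches differ, when low power is an adequate explanation.

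**Working it through.** **Inputs (Protocol article).** Morbidity p = 0.16 in each group, so the true difference is 0; margin m = 0.10; n = 273 evaluable per group; validity rate 85% (all from Number of patients needed). Two-sided 95% CI with both limits inside ±0.10 (Discussion), so z = 1.960 at each margin.

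**The plan's own figures.**
- Inflation for validity: 273 / 0.85 = 321.2, rounded up to 322; 2 × 322 = 644. This reproduces.
- Power from the stated β: 1 − 0.15 = 0.85. The stated 90% does not reproduce.

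**Power under the plan's rule.**
- SE = √(2 × 0.16 × 0.84 / 273) = 0.03138
- m / SE = 0.10 / 0.03138 = 3.187
- 3.187 − 1.960 = 1.227
- One limit inside its margin: Φ(1.227) = 0.890
- Both limits inside: 2 × Φ(1.227) − 1 = 0.780
- Chance of failing when the approaches are identical: 1 − 0.780 = 0.220

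**Sensitivity to the interval method** (95%, both limits, n = 273):

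| Method | Power |
|---|---|
| Normal formula | 78.0% |
| Exact binomial enumeration, Wald CI | 78.2% |
| Exact binomial enumeration, Newcombe CI | 77.6% |
| Farrington–Manning variance | 76.5% |
| Exact enumeration, continuity-corrected Wald CI | 73.2% |

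**Sample size the rule needs.** n = 2 × 0.16 × 0.84 × (1.960 + z)² / 0.10², where z is the normal quantile at 1 − β/2 because β is split over two margins.
- 85% power: z = 1.440, n = 310.6, so 311 evaluable; 311 / 0.85 = 365.9, so 366 enrolled per group, 732 in total.
- 90% power: z = 1.645, n = 349.3, so 350 evaluable; 350 / 0.85 = 411.8, so 412 enrolled per group, 824 in total.

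**If all 322 per group were evaluable.** SE = √(2 × 0.16 × 0.84 / 322) = 0.02889; m / SE = 3.461; power = 2 × Φ(1.501) − 1 = 0.867.

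**Other readings, to see where 273 and 90% might come from.**
- One margin only at one-sided 2.5%: 89.0% power at 273; exactly 90% would need 283.
- A 90% CI (5% per margin), both limits, no correction: 87.7% power at 273; n = 256 for 85% and 291 for 90%.
- A 90% CI, both limits, continuity correction, β = 0.15: n = 276; exact power at 273 is 84.6%.

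None gives exactly 273, and none satisfies both stated power figures.

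**If the true difference is not zero** (one group at 16%, n = 273, 95% CI, both limits):

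| Other group | Power |
|---|---|
| 18% | 66% |
| 19% | 56% |
| 14% | 72% |
| 13% | 63% |

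**The case against.** The best defence is that 273 came from a genuine equivalence calculation. With 5% per margin, β = 0.15 and a continuity correction, the formula gives 276, close to 273. On that view 85% was the intended power and 90% is a slip. This is plausible, and it shows that the one-margin explanation of the 90% is an inference, not an established fact. It does not save the plan: it corresponds to a 90% interval, while the Discussion fixes a 95% interval, and it leaves the 90% wrong.

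A second point is that α = 0.05 is the usual label for a two-sided 5% level and so sits naturally with a 95% CI. As a label that is fair. For equivalence, however, requiring a 95% interval to lie inside the margins has a type I error of 2.5%, not 5%. This is conservative for false claims of equivalence, and it is also what costs the power. The α remark is secondary to the power result.

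Third, the planned interval is stratified by ASA class, which can narrow it. The document gives no stratum rates. Assuming for illustration that 75% of patients have a 12% risk and 25% a 28% risk (16% overall), the within-stratum variance is 0.75 × 0.12 × 0.88 + 0.25 × 0.28 × 0.72 = 0.1296 against 0.1344, and power rises to about 80%. That is still short of both stated figures.

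Finally, nothing in the document says that a failed equivalence claim would be read as a difference. That is a risk of misreading. The firm consequence is a greater chance of an inconclusive trial.

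**Conclusion.** The concern holds. The sentence is impossible as written, since β = 0.15 and 90% power cannot both be true. Under the declared rule, 273 evaluable patients per group give about 78% power: 7 points below the figure that β implies and 12 points below the figure stated. The type II error is 22%, above the stated 15% and more than double the 10% that goes with 90% power.

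The 78% assumes 16% in both groups, no true difference, exactly 273 evaluable per group and no gain from stratification. Each true difference tabulated lowers it. Full evaluability would raise it to 86.7%, but the plan itself expects 85% validity. None of the two-limit 95% methods tried without stratification exceeded about 78%. How 273 was obtained cannot be established from the document, and the conclusion does not depend on it.

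**What to change.** In Number of patients needed, delete both the β of 0.15 and the 90% power, and replace the statement with wording such as: 273 evaluable patients per group give 78% power for the two-sided 95% CI of the difference to lie within ±10 percentage points when morbidity is 16% in both groups (each one-sided test at 2.5%); power is 87% if all 322 per group are evaluable. This ties the power to the rule in the Discussion and removes the ambiguity about α.

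The cost is one sentence and a less favourable figure; no patients are added. If the sponsor does want 85% or 90% power under the existing rule, restating the sentence is not enough: 311 or 350 evaluable patients per group are needed, that is 732 or 824 enrolled in total at 85% validity, against 644 planned.

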## Eligibility criteria

### Inclusion criteria

• Age ≥ 18 years

• Patients with acute cholecystitis with three of the following symptoms or signs

• Abdominal pain in the upper right quadrant

• Murphy's sign

• Leukocytosis > 10 × 10^3^/μl

• Rectal temperature > 38°C or < 36.5°C

plus

• Cholecystolithiasis (stones/sludge) or sonographic signs of cholecystitis (thickening and triple layer formation of the gall bladder wall)

• Immediate antibiotic therapy (400 mg Moxifloxacin i.v. once a day)

• Laparoscopic cholecystectomy possible within 24 hours after presentation of the patient

• Informed consent

### Exclusion criteria

• ASA IV and V (table 1)

**Table 1 T1:** ASA-Criteria

***ASA Physical Status (PS) Classification System from the American Society of Anesthesiologists***	
***ASA PS Category***	***Preoperative Health Status***

ASA PS 1	Normal healthy patient
ASA PS 2	Patients with mild systemic disease
ASA PS 3	Patients with severe systemic disease
ASA PS 4	Patients with severe systemic disease that is a constant threat to life
ASA PS 5	Moribund patients who are not expected to survive without the operation
ASA PS 6	A declared brain-dead patient who organs are being removed for donor purposes

American Society of Anesthesiologists (ASA) Physical Status (PS) Classification System. Categories to classify the preoperative health status of patients.

• Septic shock

• Perforation or abscess of the gall bladder

• No possibility of laparoscopic surgery

• Additional antibiotics needed for secondary disease

• Intolerance to moxifloxacin or other quinolones

• Pregnancy (also suspected), breast feeding

• Life-expectancy < 48 hours

• End-stage liver disease (Child-Pugh C)

• Psychiatric or severe neurologic disease

• Relevant bradycardia or other symptomatic arrhythmias

• Significant cardiac disease

• Disorder with QT prolongation

• Hypocalcaemia or other electrolyte disorders

• Earlier participation in this trial

## Ethics, Study Registration and Consent

The final protocol was approved by the independent ethics committee of the University of Heidelberg. The study was registered at ClinicalTrials.gov (NCT00447304). Patients who are scheduled for laparoscopic cholecystectomy (immediate or elective) due to acute cholecystitis are informed about the trial (laparoscopic surgery, possibility of conversion to open surgery, other risks, benefits and confidential handling of documented findings) and are given the opportunity to participate at the screening visit. Informed consent is required. Patients may withdraw from the study at any time without giving reasons and without jeopardizing their further treatment. The investigator may also withdraw patients if this is in their best interests.

## Randomisation and procedures for minimizing bias

This study is randomized to minimize bias. Sealed randomization envelopes are provided in packs of four by the CRO and are held centrally at each investigational site. An envelope is opened when a patient agrees to take part and patients are informed whether they are to be treated with immediate surgery or initial conservative antibiotic therapy.

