## Study organization

All eligible patients are seen by a gastroenterologist or surgeon and are enrolled after giving informed consent. The incidence of patients with acute cholecystitis ranges from 10 to >100 per year at different investigational sites. With about 30 sites, it is estimated that enrollment of 644 patients will take about 24 months. All findings are recorded in the patients medical records and CRF provided for this study by the investigator. Data verification is performed by the CRO, who will also perform the analysis on the locked database after plausibility testing and data query correction.

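### Envelopes held at sites in packs of four in an open trial may let staff infer up to one third of allocations beforehand, if each pack is balanced and used in order

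*Protocol article*

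**What the plan says.** The section *Randomisation and procedures for minimizing bias* reads: "Sealed randomization envelopes are provided in packs of four by the CRO and are held centrally at each investigational site". It continues: "An envelope is opened when a patient agrees to take part and patients are informed whether they are to be treated with immediate surgery"; the other possible assignment is the antibiotic-first arm. *Organization of the study* calls the trial a "multicenter, prospective, randomized non-blinded study", and the *Design* part of the Abstract also says it is not blinded.

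Three other places bear on the point:

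- *Immediate surgery versus conservative procedure with subsequent elective surgery* says of usual practice: "The approach taken is often decided by whether the patient first sees a gastroenterologist", who favours the conservative route, or a surgeon, who favours immediate surgery.
- *Study organization* says that these same two specialties see the eligible patients, and adds: "With about 30 sites, it is estimated that enrollment of 644 patients will take about 24 months".
- *Number of patients needed* sets equal groups: "322 patients are required per group, resulting in a total patient sample of 644".

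The article does not say how many envelopes per arm a pack holds, whether a pack is a randomisation block, or whether packs are opened strictly in order.

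**The concern.** Sealing an envelope hides its content. It does not hide what can be deduced from the envelopes already opened. In an open trial the site learns every earlier assignment, and a pack of four shows where the count restarts. If packs are balanced, the last envelope of each pack, and sometimes the last two, can be known before a patient is invited. Opening the envelope only after agreement does not help, because the decision whom to invite comes before it.

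The article itself supplies a motive and an opportunity. The two enrolling specialties lean towards opposite arms. Several eligibility items rest on judgement: whether laparoscopic surgery is feasible within 24 hours, whether laparoscopy is impossible, and whether cardiac disease is significant. Such items can be read more or less strictly according to the arm expected next. The result would be arms that differ in prognosis at entry. That could hide a true difference in morbidity or create a false one, in a trial whose conclusion depends on the 95% confidence interval lying within ±10 points.

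**Working it through.** The article gives no figure for predictability, so there is none to reproduce.

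**Inputs**

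- Envelopes per pack: 4 (*Randomisation and procedures for minimizing bias*).
- Allocation ratio: 1:1, inferred from 322 per group (*Number of patients needed*).
- Total and sites: 644 patients, about 30 sites (*Study organization*).
- Assumption, not stated in the article: each pack holds two envelopes per arm, packs are used in order, and staff keep track of earlier allocations.

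**Step 1: allocations known with certainty.** A balanced pack has 6 equally likely sequences. An allocation is certain once only one arm is left in the pack.

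- AABB and BBAA: positions 3 and 4 are certain, so 2 each.
- ABAB, ABBA, BAAB and BABA: only position 4 is certain, so 1 each.

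Expected number per pack = (2×2 + 4×1)/6 = 8/6 = 1.333, and 1.333/4 = 33.3%. Position 4 is always known; position 3 is known with probability 2/6 = 1/3.

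**Step 2: best guess.** The observer always guesses the arm with more envelopes left. The chance of being right by position is:

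- position 1: 1/2
- position 2: 2/3
- position 3: 1/3×1 + 2/3×1/2 = 2/3
- position 4: 1

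The sum is 17/6 = 2.833 of 4, or 70.8%. Simple randomisation gives 50%.

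**Step 3: scale in this trial.**

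- Ceiling, with every pack completed: 644/3 = 214.7, about 215.
- Average site: 644/30 = 21.5 patients, that is 5 full packs plus 1 to 2 patients. The extra patients fall in positions 1 and 2, which are never certain. So 5 × 1.333 = 6.7 per site, 6.7/21.5 = 31%, and 30 × 5 × 1.333 = 200 in all.
- Range over the assumption: if packs are not balanced the share falls, to 0% under simple randomisation.

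**Step 4: alternatives.** The fixed sizes were enumerated exactly. The mixed sizes were simulated (3,000 sequences of 24) for an observer who knows that the sizes are 4 and 6 but not their order.

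| Scheme | Certain | Best guess right |
|---|---|---|
| Fixed blocks of 4 | 33.3% | 70.8% |
| Fixed blocks of 6 | 25.0% | 68.3% |
| Fixed blocks of 8 | 20.0% | 66.6% |
| Sizes 4 and 6 at random | 5.7% | 68.6% |
| Simple randomisation | 0% | 50% |

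**Step 5: an illustration against the margin.** At 16% morbidity and 273 per group, the 95% half-width is 1.96 × √(2 × 0.16 × 0.84/273) = 6.15 points. With truly equal arms that leaves 10 − 6.15 = 3.85 points. If every certain allocation (one third) were steered, the patients entered under the two known arms would have to differ in risk by 3.85 × 3 = 11.5 points to use this up. That is a worst case; the documents do not show how much steering would occur.

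**The case against.** The strongest reply is that the predictability is partly inferred. The article describes packs, not blocks. A pack could be only a supply unit, and a condensed article commonly leaves sequence generation, numbering and opacity of envelopes to the full protocol. A reader might infer that one third of allocations are certain in advance as a plain fact. The text does not support that without the balance and order assumptions. What it does fix is the pack size, storage at the site and the open design, and those make the question a fair one.

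Four further points carry weight:

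- The count of 215 is a ceiling. Unfinished packs lower it, as would separate packs per ASA class if they are used. Staff would also have to track allocations at fewer than one patient a month per site.
- Patients present acutely and surgery must be feasible within 24 hours, so holding a patient back for a later envelope is hardly practicable. Selective invitation is the main route left.
- The two specialties' preferences run in opposite directions and both enrol, so no consistent direction of bias is shown.
- The *Discussion* stratifies the principal analysis and the confidence interval by ASA class. This deals with part of any imbalance in severity, but not with selection within a class.

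A reader might go further and conclude that comparability is broken and that no analysis could repair it. The documents show a way in for bias, not its occurrence, and the stratified analysis is a partial correction.

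**Conclusion.** The point stands as a conditional weakness of design. Visible packs of four, kept at the site of an open trial, let staff infer later allocations if each pack is balanced and packs are used in order. Under those assumptions up to 33% of allocations are certain beforehand (at most about 215 of 644, about 200 at the average site size), and the best guess is right 71% of the time. If packs are unbalanced the share is lower and may be zero. The enrolling specialties' opposite preferences and the judgement-based eligibility items make selective invitation possible, and the ASA stratification can correct it only partly. Neither the amount nor the direction of any resulting bias can be derived from the documents. The change is worth making because it is cheap.

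**What to change.** For patients not yet randomised, the CRO should replace the packs of four with one continuous, sequentially numbered series of envelopes per site, built from randomly varying block sizes that are neither disclosed to sites nor published. With sizes 4 and 6 this cuts certain allocations from 33% to about 6%. Best-guess success falls only from 71% to about 69%, so the change removes most of the certainty but little of the guessing advantage. The cost is a new list and envelope set, and a slightly larger possible imbalance within a site.

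As an option, the CRO could release each allocation, by telephone or fax, only after eligibility and consent have been logged. This has a real added cost, since the service would have to run for emergency admissions at about 30 sites.
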